## Abstract

**Background:**

Hazardous alcohol consumption is a leading modifiable cause of mortality and morbidity among young people. Screening and brief intervention (SBI) is a key strategy to reduce alcohol-related harm in the community, and web-based approaches (e-SBI) have advantages over practitioner-delivered approaches, being cheaper, more acceptable, administrable remotely and infinitely scalable. An efficacy trial in a university population showed a 10-minute intervention could reduce drinking by 11% for 6 months or more among 17-24 year-old undergraduate hazardous drinkers. The e-SBINZ study is designed to examine the effectiveness of e-SBI across a range of universities and among Māori and non-Māori students in New Zealand.

**Methods/Design:**

The e-SBINZ study comprises two parallel, double blind, multi-site, individually randomised controlled trials. This paper outlines the background and design of the trial, which is recruiting 17-24 year-old students from seven of New Zealand's eight universities. Māori and non-Māori students are being sampled separately and are invited by e-mail to complete a web questionnaire including the AUDIT-C. Those who score >4 will be randomly allocated to no further contact until follow-up (control) or to assessment and personalised feedback (intervention) via computer. Follow-up assessment will occur 5 months later in second semester. Recruitment, consent, randomisation, intervention and follow-up are all online. Primary outcomes are (i) total alcohol consumption, (ii) frequency of drinking, (iii) amount consumed per typical drinking occasion, (iv) the proportions exceeding medical guidelines for acute and chronic harm, and (v) scores on an academic problems scale.

**Discussion:**

The trial will provide information on the effectiveness of e-SBI in reducing hazardous alcohol consumption across diverse university student populations with separate effect estimates for Māori and non-Māori students.

**Trial registration:**

Australian New Zealand Clinical Trials Registry (ANZCTR) ACTRN12610000279022

## Background

Hazardous alcohol consumption is a leading cause of mortality and morbidity in high and middle income countries and an increasing problem in low income countries [1,2]. In an era in which state controls on the availability of alcohol have dramatically decreased [3], effective interventions to reduce demand for alcohol, that are deliverable to many, are needed.

Screening and brief intervention (SBI), involving the systematic identification of people with hazardous alcohol consumption and the provision of brief advice on how to reduce this, is now accepted as a key plank of public policy to reduce alcohol-related harm in the community. A meta-analysis of opportunistic SBI, which examined the outcomes of 34 randomised controlled trials, revealed significant reductions in consumption and alcohol-related problems [4].

Web-based screening and brief intervention (e-SBI) has certain advantages over practitioner-delivered SBI: it involves little or no clinician contact and it can be conducted anonymously. Additionally, e-SBI may be more acceptable to many drinkers than a face-to-face intervention [5]. While various computerized methods for delivering SBI have been developed [6,7], there had, until recently, been no rigorous efficacy trials of these interventions published in the scientific literature [8].

### Hazardous alcohol use among university students

University students have been found to have considerably riskier drinking patterns than their non-student peers [9-11]. For example, in New Zealand, a random sample of students (response rate 82%) from one large public university were found to have a prevalence of hazardous drinking (a score of 8 or higher on the Alcohol Use Disorders Identification Test; AUDIT[12]), which was double that of their peers in the general population [9]. The prevalence of harmful drinking, as indicated by a score of 15 or higher on the AUDIT, was three times higher than that among their non-student peers.

### Previous research on e-SBI

On the basis of extensive development research conducted at a university student health service in New Zealand [13,14], a first randomised controlled trial involving 104 participants was conducted in 2002. Students who screened positive for hazardous drinking (AUDIT ≥ 8) at an initial assessment, conducted electronically in the reception area, were randomly assigned to a leaflet-only control group or to receive an assessment and personalised feedback intervention, delivered entirely via the Internet [15]. This took an average of 15 minutes and was completed during the waiting time to see medical staff. Participants were followed up after six weeks and again after six months. Relative to controls, those who received the intervention drank 26% less alcohol after six weeks and had 24% fewer problems six months later [16].

These promising results were confirmed in the next trial of e-SBI, in which 1,010 students were screened over a 3 week period in the reception area and 576 were randomised to intervention or control groups. Participants were re-assessed 6 and 12 months later, with 85% retention. The effects were similar to those of the first trial [17]. At six months, relative to controls, patients receiving e-SBI reported significantly lower drinking frequency (-21%), lower total consumption (-23%), and fewer academic problems (-24%). Encouragingly, intervention effects endured. At 12 months, significant differences in total consumption (-23%; equivalent to 3.5 standard drinks per week) and academic problems (-20%) remained, and AUDIT scores were 2.2 points lower than those of controls [17].

This reduction in AUDIT score was estimated to be equivalent to an absolute risk reduction of 9% (95% CI 3% to 14%) in diagnoses of alcohol abuse and dependence [18]. Assuming the program could be implemented with 50% of the New Zealand student population, this equates to 1,424 cases of alcohol use disorders prevented per year, a significant public health benefit. A clear limitation of the primary care based delivery of e-SBI is that in many universities the student health service does not provide healthcare to the majority of the student population. Accordingly, to realise the population-level benefits of e-SBI, a pro-active case finding approach would be required.

To address this limitation, a third trial was conducted at an Australian university, where we sought to determine whether an e-SBI program called THRIVE (Tertiary Health Research Intervention Via E-mail) could be delivered on the basis of a universal screening program, i.e., by-passing the primary care setting. In addition to circumventing the problems of interfacing with a busy primary care service, the approach takes advantage of the economy of scale that can be achieved with the Internet, making it possible to offer assistance to thousands of students at low cost, including many who would not routinely come into contact with health services of any kind.

We invited 13,000 17-24 year-old students to complete a web-based AUDIT and 7,237 responded [19]. A third (n = 2,435) scored in the hazardous/harmful range (≥ 8) and were randomised to THRIVE or screening alone, and 2,050 (80%) completed at least one follow-up assessment. Intervention, delivered immediately following the assessment, consisted of 10 minutes of web-based assessment and personalised feedback. After one month, participants receiving intervention drank significantly less often (-11%), smaller quantities per occasion (-7%) and consumed a lower volume of alcohol overall (-17%), than did controls. At six months, intervention effects persisted for drinking frequency (-9%) and volume of alcohol consumption (-11%) [20].

Overall, the effects seen in the New Zealand trials were replicated but were somewhat smaller in the THRIVE trial. Nonetheless, given the reach of the intervention delivered on the basis of universal screening, THRIVE has greater potential to produce a population effect than primary-care based delivery of e-SBI.

### The need for large effectiveness trials

We are at the stage when there is a pressing need for large effectiveness trials. There being several recent trials conducted among university students, however, much of the research has been conducted in conditions which would generalise poorly to practice, and, with one exception, a study whose results are yet to be published [21], there have been no large, multi-site effectiveness trials. Trialling the intervention across multiple sites has the advantages of testing the robustness of its effects across different student drinking cultures, which national surveys have shown to vary in levels of consumption [22] and exposure to alcohol outlets [23] and promotion [24].

In addition to being firmly rooted in the experience of three previous clinical trials, the proposed study is based on extensive experience in surveying university student drinking via the Internet. In 2005 a web survey (response rate 65%) was conducted with large random samples of students from six New Zealand university campuses [22]. The survey was repeated in 2007 at eight campuses (response rate 68%). New Zealand is now uniquely placed in having up-to-date national student alcohol consumption data (from the 2005 and 2007 student surveys) on which to base the proposed intervention.

### Responsiveness to Māori health

New Zealand was founded on the basis of a treaty between the indigenous (Māori) peoples and those, largely from Great Britain [as it was then], who were part of the colonial expansion of European peoples. The Treaty of Waitangi, signed in 1840, and recognised as the founding document of New Zealand, grants to Māori the rights and privileges of British subjects.

The alcohol research undertaken among New Zealand university students has been conducted within a Māori health or Treaty framework. Accordingly, we adopted an Equal Explanatory Power model [25] for the national student surveys. We sought to invite equal numbers of Māori and non-Māori students from each campus in order to maximize the explanatory power of the study for Māori, who have traditionally been poorly served by population surveys, despite bearing a considerably greater burden of alcohol-related harm than non-Māori [26]. We have maintained this approach in the trial design, described below.

## Aim

The aim is to determine the effectiveness of e-SBI for Māori and non-Māori university students in New Zealand.

## Methods/Design

### Design

The study consists of two parallel, multi-site, double blind, individually randomised controlled trials. The trials are recruiting Māori and non-Māori students aged 17-24 years from seven of New Zealand's eight universities. Figure 1 shows the trial design.

**Figure 1 F1:**
[figure not shown]
**e-SBINZ trial design**.

### Sampling

In cooperation with each university administration, we have drawn random samples of undergraduates aged 17-24 years. This was done separately for Māori and non-Māori participants on the basis of self-reported ethnicity in university enrolment forms. The aim was to have equal numbers of Māori and non-Māori enrolled, however, that was impossible to achieve on some campuses, given low enrolments of Māori. In such campuses, we have invited all Māori in the requisite age group to participate and we increased the numbers of Māori invited from other universities accordingly.

### Recruitment

We have adapted a survey recruitment approach that has been used extensively and which has been described in detail elsewhere [27,28]. Four weeks after the start of the first semester random samples of students aged 17-24 years will be sent an e-mail containing a hyperlink to a web questionnaire. Up to three reminder e-mails will be sent in the following weeks to non-respondents.

### Instrument, randomisation, and intervention

Respondents will visit the study website and be presented with an introductory page followed by one page of five questions concerning (1) gender, (2) age, and the three items of the AUDIT-Consumption subscale [12]: (3) frequency of drinking; (4) number of standard drinks (defined as containing 10 g ethanol) consumed per typical drinking occasion; and (5) frequency of having six or more drinks per occasion. The AUDIT consumption subscale (AUDIT-C) is a valid screening tool, with specificity and sensitivity similar to the full AUDIT [29] and its psychometric performance has been previously evaluated in online studies with university students [30].

Upon clicking the submit button on this page, AUDIT-C scores will be calculated. Those who score ≥ 4 on the AUDIT-C will be randomly allocated by the web server to either the intervention or control group. The control group will be sent to a *Thanks *page at this point and advised that they will be contacted again by e-mail in second semester to complete a similar brief questionnaire.

The rationale for limiting the control group's alcohol questions to three items is that previous research shows that simply asking questions about alcohol consumption can act as intervention, producing reductions in self-reported drinking levels [31]. Indeed, such effects have been shown for the AUDIT alone [32].

Those in the intervention group will continue and be asked AUDIT items 4-10, and additional questions concerning the largest number of standard drinks consumed on one occasion in the last four weeks, the duration of the drinking episode in hours, and their body weight (for the purpose of estimating peak blood alcohol concentration). They will also complete the Leeds Dependence Questionnaire (LDQ; 10 items) [33]. The psychometric performance online of both the AUDIT and the LDQ has been confirmed in previous study with university students [34].

The intervention group will then receive personalised feedback consisting of: their AUDIT score and an LDQ score with an explanation of the associated health risk and information about how to reduce that risk; an estimated blood alcohol concentration (BAC) for the respondent's heaviest episode in the previous four weeks, with information on the behavioural and physiological sequelae of various BACs, and traffic crash relative risk; estimates of monetary expenditure per month; bar graphs comparing episodic and weekly consumption with that of other students and members of the general population of the same age and gender; and hyperlinks for help with drinking problems. Further web pages will be presented as options, offering facts about alcohol, tips for reducing the risk of alcohol-related harm, and where medical help and counselling support can be found. A demonstration version of the instrument can be viewed at http://ipru3.otago.ac.nz/limesurvey/.

### Follow-up

A high follow-up rate is clearly vital to the success of e-SBI trials and several approaches have been adopted to maximise this. In the second semester, approximately five months later, all participants will be invited to complete a brief on-line follow-up assessment, with the chance to win a $500 supermarket voucher or an Apple iPad. The assessment will include questions concerning the frequency of drinking and amount consumed per typical drinking occasion, all with a reference period of the last 4 weeks. In addition, participants will be presented with the five questions comprising the Academic Role Expectations and Alcohol Scale (AREAS) [35], plus questions concerning their subjective experience of the study.

### Blinding

Study participants will be unaware that they are involved in a trial, and that they have been randomised. They will have consented to complete a web survey of "the experiences of tertiary students with alcohol over time". The attention of the intervention group will not be drawn to the attempt to influence their behaviour. These decisions both serve to minimise bias relating to assessment reactivity and other aspects of study participation [36,37] and are also congruent with the aspiration to undertake the study in conditions as close as possible to those in which it would be routinely delivered.

### Sample size estimation

The same sample size will be sought separately for Māori and non-Māori students. The estimate is based on the following parameters and assumptions.

#### Sample size required for analysis at follow-up

We used as the basis for the estimate, the mean volume of alcohol reported at the 6 month follow-up THRIVE trial [38], namely 16.1 drinks (SD 15.9) for the control group and 13.6 drinks (SD 14.0) for the intervention group. Assuming a 5% level of significance, 80% power and a dispersion factor of 0.92 to reflect the skew in this measure [39], we would require 547 participants per group at follow-up in the proposed trial.

#### Attrition

Given the need for 1,094 cases (547 per group) to be analysed at follow-up, 1,563 individuals will have to be randomised at baseline (to either the intervention or control group), assuming attrition of 30% [1600/(1-0.3)]. This is considered realistic given the 6-month follow-up rate achieved in the THRIVE trial of 65% [38] and the fact that higher levels of participation were accomplished in our New Zealand research in this population (85% at 12 months) [17]. In addition, specific attention will be given to reducing attrition in the proposed study, including e-mail messages to non-respondents with two questions concerning the frequency of drinking and typical occasion quantity in the last four weeks--to be answered in the body of an e-mail message--from which modelling of attrition bias will be based [40].

#### Screening and consent

Given the need for 1,563 individuals to be allocated at baseline, we will seek consent for follow-up from 3,126 individuals, allowing for a 50% rate of screening negative or refusing consent for follow-up. This is informed by the proportion of New Zealand students who scored in the positive range in the national surveys (65%) [9].

#### Number to be invited to participate

The response rate in the THRIVE trial was 57%. Accordingly, on the conservative assumption that 40% agree to participate, we will need to invite 7,814 Māori and 7,814 non-Māori individuals. Given participation from seven universities we would therefore seek to invite 1,116 Māori and 1,116 non-Māori from each university.

### Outcomes

The primary outcomes are (1) volume of alcohol consumed per week, (2) frequency of drinking (occasions per week), (3) amount consumed per typical drinking occasion, (4) the proportion who exceed New Zealand recommended upper limits for: risk of acute harm (no more than 4 drinks per occasion for women; no more than 6 drinks per occasion for men); and (5) risk of chronic harm (no more than 14 drinks per week for women; no more than 21 drinks per week for men); and (6) scores on the AREAS [35].

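### Six outcomes are all primary with no ranking or success rule, while each trial is sized on weekly volume alone at an unadjusted 5%

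*Protocol article*

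**What the plan says.** The Outcomes section lists the primary outcomes as a numbered series. It begins "The primary outcomes are (1) volume of alcohol consumed per week, (2) frequency of drinking (occasions per week", continues with the typical amount per occasion and the two proportions above the acute-harm and chronic-harm limits, and ends at "6) scores on the AREAS [35". The Abstract gives the same six under five labels, starting "Primary outcomes are (i) total alcohol consumption, (ii) frequency of drinking" and combining the two limits in one item: "iv) the proportions exceeding medical guidelines for acute and chronic harm, and (v) scores on an academic problems scale". Neither list ranks the outcomes or says how many must succeed.

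The Analysis section assigns a regression model to each type of outcome. It gives no test order, adjustment or success rule.

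The sample size section uses one outcome, "the mean volume of alcohol reported at the 6 month follow-up THRIVE trial", with planning values of "16.1 drinks (SD 15.9) for the control group and 13.6 drinks (SD 14.0) for the intervention group". The error rates are set there: "Assuming a 5% level of significance, 80% power and a dispersion factor of 0.92 to reflect the skew in this measure". The result is 547 per group at follow-up, and the same size is sought for the Māori and the non-Māori trial.

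**The concern.** The list of primary outcomes and the sample size do not match. Six outcomes are declared primary, but the significance level and power are spent on one. If the other five are also tested at 5%, each adds a chance of a false-positive primary result.

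The outcomes also overlap. The Follow-up section names only drinking frequency and typical quantity as drinking questions, plus AREAS. Volume therefore appears to be built from frequency and quantity, and the two limit outcomes appear to be cut-points on quantity and volume.

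Split results are likely. The article's account of the earlier Australian trial reports effects on frequency, quantity and volume at one month, but persistence at six months only for frequency and volume. Nothing in this plan says how such a pattern would be read, although the Discussion says the findings could inform a decision on implementation in each population.

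**Working it through.** **Inputs.** From the sample size section: means 16.1 and 13.6, dispersion 0.92, significance level 5% (taken as two-sided, since sidedness is not stated), power 80%, 547 per group. From the Outcomes section: six primary outcomes.

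**1. The plan's own figure.** The negative binomial formula for two groups is

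n = (z₀.₉₇₅ + z₀.₈₀)² × [(1/μ₁ + k) + (1/μ₂ + k)] / [ln(μ₁/μ₂)]²

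- (1.960 + 0.842)² = 7.849
- 1/16.1 + 1/13.6 + 2 × 0.92 = 1.976
- ln(16.1/13.6) = 0.1687, squared 0.02848
- n = 7.849 × 1.976 / 0.02848 ≈ 544.5, so 545 per group

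This agrees closely with 547. At 547 the standard error of the log ratio is √(1.976/547) = 0.0601, so the standardised effect is 0.1687/0.0601 = 2.808. Power is Φ(2.808 − 1.960) = 80.2%. The stated size therefore uses the whole 5% on volume.

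**2. Familywise error per trial, six tests at 5%, any one counted.**

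| Assumption about the six outcomes | Chance of at least one false positive |
|---|---|
| Independent: 1 − 0.95⁶ | 26.5% |
| Common correlation 0.3 | 24.1% |
| Common correlation 0.5 | 20.7% |
| Common correlation 0.6 | 18.6% |
| Common correlation 0.7 | 16.4% |
| Common correlation 0.8 | 13.9% |
| Common correlation 0.9 | 10.8% |

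The correlated rows come from simulating 1,000,000 sets of six correlated two-sided z tests.

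**3. Structured overlap.** Two assumed models set volume = frequency × quantity, derive two threshold outcomes, and add a correlated AREAS score.

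- 6,000 null trials per setting at 547 per group, with frequency-quantity correlation from 0 to 0.5: 21.6%, 20.8% and 20.4%.
- Correlations derived from log-normal frequency and quantity, with frequency-quantity correlation 0 to 0.4 and AREAS correlation 0.1 or 0.3: 20.8% to 22.1%.

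**4. Price of an equal split.** Bonferroni gives 0.05/6 = 0.00833, with critical value 2.638. Power for volume at 547 per group is Φ(2.808 − 2.638) = 56.7%. Restoring 80% needs (2.638 + 0.842)² × 1.976 / 0.02848 ≈ 840.1, so 841 per group.

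**5. Price of an order.** If volume is the only primary outcome, or the first in a fixed sequence, it is tested at the full 5% and keeps the 80.2% of step 1.

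**The case against.** The strongest reply is that this is a journal article and the analysis plan is not shown. Test order and multiplicity rules are commonly left to that plan. Volume is listed first and sized at the full 5%, which fits a fixed sequence starting with volume. The article also stresses separate effect estimates and replication rather than a single significance verdict.

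Much of this stands. A reader might infer that the trial has no error control anywhere, or that it has adopted a rule under which any one of six results suffices. The documents support neither: the analysis plan is unseen, no success rule is written, and 5% appears only in the sample size section. If success required all six to be significant, there would be no inflation at all, but that rule is not written either.

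What does not fall away is the designation itself. The article fixes which outcomes are primary and what the trial is sized for, and the two disagree. An analysis plan that split the 5% would undercut the stated 80% power. One that ordered or demoted outcomes would add a ranking that the published list lacks.

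**Conclusion.** The concern holds in a limited form. Six unranked primary outcomes do not match a sample size that spends the full 5% on one. Under the inferred reading (each tested at 5%, any one counted), familywise error per trial is well above 5% at every correlation examined, from about 11% to 26.5%.

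A reader might quote 20-26% as the error rate. The documents do not support that as a fact. They give no correlations, 26.5% needs an independence that the overlap of the outcomes rules out, and 20% is not a floor. About 20-22% is the result of assumed models only.

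A reader might also add up the error over both trials. That is not apt, because the trials are sized separately and are to give separate estimates for Māori and non-Māori students. The relevant family is the set of primary outcomes within one trial.

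The 57% power figure depends less on assumption: it follows from the plan's own inputs, with a two-sided Bonferroni test.

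**What to change.** Make one of these changes in the protocol, the analysis plan and the registry entry, dated before any follow-up data are seen.

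- **Preferred:** name weekly volume as the single primary outcome in each trial and make the other five secondary. Power for volume stays at about 80% with 547 per group.
- **Equally sound:** keep all six primary in a prespecified fixed sequence that starts with volume, each tested at 5% only if all earlier ones are significant. Power for volume is again about 80%. The full order must be written down.
- **If six unordered primary outcomes must stay:** control familywise error within each trial. Under Bonferroni, use 0.05/6 with 99.17% intervals and restate the power for volume as about 57%. Under Holm, 57% is a lower bound.

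The first two options need no extra participants, and under all three every outcome is still measured and reported. The cost is that five outcomes lose primary status or depend on earlier tests, or else the stated power falls. Because the article describes recruitment as under way, the change should be recorded as a dated amendment with its reason.
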